**Severe Pneumonia**

Fever is associated with severe dyspnea, respiratory distress, tachypnea (> 30 breaths/min), and hypoxia (SpO2 < 90% on room air). However, the fever symptom must be interpreted carefully as even in severe forms of the disease, it can be moderate or even absent. Cyanosis can occur in children. In this definition, the diagnosis is clinical, and radiologic imaging is used for excluding complications.

**Acute Respiratory Distress Syndrome (ARDS)**

The diagnosis requires clinical and ventilatory criteria. This syndrome is suggestive of a serious new-onset respiratory failure or for worsening of an already identified respiratory picture. Different forms of ARDS are distinguished based on the degree of hypoxia. The reference parameter is the PaO2/FiO2:

- Mild ARDS: 200 mmHg < PaO2/FiO2 ≤ 300 mmHg. In not-ventilated patients or in those managed through non-invasive ventilation (NIV) by using positive end-expiratorypressure (PEEP) or a continuous positive airway pressure (CPAP) ≥ 5 cmH2O.
- Moderate ARDS: 100 mmHg < PaO2/FiO2 ≤ 200 mmHg.
- Severe ARDS: PaO2/FiO2 ≤ 100 mmHg.

When PaO2 is not available, a ratio SpO2/FiO2 ≤ 315 is suggestive of ARDS.

Chest imaging utilized includes chest radiograph, CT scan, or lung ultrasound demonstrating bilateral opacities (lung infiltrates > 50%), not fully explained by effusions, lobar, or lung collapse.

**Clinical improvement Criteria**

1. Body temperature remains normal for at least 3 days (ear temperature is lower than 37.5 °C).

2. Respiratory symptoms are significantly improved.

3. Lung imaging shows obvious improvement in lesions.

4. There is no co-morbidities or complications which require hospitalization.

5. SpO2, >93% without assisted oxygen inhalation.

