**Inclusion Criteria:**

- At least 18 years of age
- COVID-19 infection, confirmed by polymerase chain reaction (PCR) test
- Mild to moderate COVID-19 infection

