**Primary Outcome Measure:**

- 1. Duration required to have clinical improvement

[Time Frame: 1 months]

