**Uncomplicated (mild) Illness**

These patients usually present with symptoms of an upper respiratory tract viral infection, including mild fever, cough (dry), sore throat, nasal congestion, malaise, headache, muscle pain, or malaise. Signs and symptoms of a more serious disease, such as dyspnea, are not present.

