**Radio-Imaging**

| **Trait** | **Findings** |
| --- | --- |
| Chest X-Ray  CT Chest | Normal/ Consolidation ( unilateral or bilateral) / Patchy opacity  Consolidation/ Ground Glass Opacity/nodule/ multifocal |

Post COVID symptoms:

Principal Investigators: ……………….. Date:

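### The primary endpoint's imaging criterion cannot be met by eligible mild patients with clear lungs, and the case record form as designed cannot date it for any patient

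*Protocol*

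**What the plan says.** The Primary Outcome Measure section names one outcome, "Duration required to have clinical improvement", with "Time Frame: 1 months". The Data analysis section plans a Kaplan-Meier curve for the duration of recovery.

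The operational definition headed Clinical improvement Criteria has five numbered items:

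1. normal temperature for at least three days;
2. significant improvement in respiratory symptoms;
3. "Lung imaging shows obvious improvement in lesions";
4. "There is no co-morbidities or complications which require hospitalization";
5. oxygen saturation above 93% without assisted oxygen.

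The list does not say whether all five must hold, and item 3 makes no exception for patients without lesions.

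The Inclusion Criteria admit "Mild to moderate COVID-19 infection". On mild illness the operational definition says "These patients usually present with symptoms of an upper respiratory tract viral infection" and "Signs and symptoms of a more serious disease, such as dyspnea, are not present". It requires no imaging finding.

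In the Case Record Form, symptoms, temperature and oxygen saturation have daily columns to day 30. Laboratory tests have columns for admission and days 3, 5, 7, 10 and 14. The Radio-Imaging table has a single findings cell, and its chest X-ray options are "Normal/ Consolidation ( unilateral or bilateral) / Patchy opacity". Comorbidity is entered once, as a list of diagnoses.

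**The concern.** A time-to-event outcome needs an event that every patient at risk can have, and a date for it. Criterion 3 fails on both counts. A patient with a normal baseline image has no lesion that could improve, and one undated image cannot show change or say when it happened.

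Whoever derives the outcome must then choose: leave clear-lung patients without an event to the end of follow-up, treat criterion 3 as met, or ignore it. The protocol supports none of these over the others, and each gives a different Kaplan-Meier curve. At stake are the absolute improvement rates and durations, the link to the planning assumptions and, under a further condition shown below, the blood-group comparison itself.

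**Working it through.** **Can each criterion be dated from the Case Record Form?**

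| Criterion | What the form records | Datable? |
|---|---|---|
| 1 Temperature | Daily to day 30 | Yes |
| 2 Respiratory symptoms | Daily yes/no to day 30 | Yes, once a rule for improvement is stated |
| 3 Imaging | One findings cell; no date, repeat or change category | No, for any patient |
| 4 Comorbidity or complication needing hospitalization | Comorbidity list once; no item on need for hospital care | No |
| 5 Saturation without oxygen | Daily saturation; no oxygen-support field | Only in part |

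If all five are required, no event date can be derived from the form as designed.

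**The plan's own figure.** The inputs, from Sample size, are p1 = 0.70 (A) and p2 = 0.90 (non-A) cured by day 12, two-sided 0.05, power 90%, and a 1:2 ratio. With p* = 0.80 and r = 1/2 (group 1 over group 2):

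n = [(r+1)/r] × p*(1−p*) × (Zβ + Zα/2)² / (p1−p2)² = 3 × 0.16 × (1.2816 + 1.9600)² / 0.04 = 126.1.

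Taking this as the smaller group gives 126 + 252 = 378, and 378 × 1.1 = 416. The stated totals are reproduced. They serve here only as group sizes for the illustration.

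**Effect of criterion 3 as written.** Let f be the share with clear lungs. The documents do not give it, so a range is shown. These patients never have the event, so the ceiling on observed improvement is 1 − f. The planned 0.90 is impossible when 1 − f < 0.90, that is f > 0.10, and the planned 0.70 when f > 0.30.

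Suppose f is equal in both groups and the planning rates hold in the remaining patients. The observed rates are then 0.70(1−f) and 0.90(1−f), here called a and b. With n1 = 126, n2 = 252 and pooled proportion p̄:

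power = Φ{ [|a−b| − 1.96 √(p̄(1−p̄)(1/n1+1/n2))] / √(a(1−a)/n1 + b(1−b)/n2) }

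| f | Ceiling | A | non-A | Difference | RR | Power |
|---|---|---|---|---|---|---|
| 0 | 1.00 | 0.70 | 0.90 | 0.20 | 0.778 | 99.6% |
| 0.10 | 0.90 | 0.63 | 0.81 | 0.18 | 0.778 | 96.1% |
| 0.20 | 0.80 | 0.56 | 0.72 | 0.16 | 0.778 | 87.0% |
| 0.40 | 0.60 | 0.42 | 0.54 | 0.12 | 0.778 | 59.6% |

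The relative risk does not move, because (1−f) cancels.

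**If f differs by blood group.** Take no true difference, with 0.90 in both groups among patients with lesions. With f = 0.20 in A and 0.30 in non-A, the rates are 0.90 × 0.80 = 0.72 and 0.90 × 0.70 = 0.63, so RR = 1.14, and the test rejects about 41% of the time. With f = 0.20 and 0.40, the rates are 0.72 and 0.54, so RR = 1.33, rejected about 93% of the time. Nothing in the documents shows that imaging status differs by blood group, so this states a condition and does not predict a result.

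**The case against.** The strongest reply has three parts.

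- The list never says that all five criteria are required. Scoring a criterion that does not apply is often left to a statistical analysis plan, which may exist. That is fair as far as it goes: an analysis plan could settle the scoring for clear lungs, but it could not supply image dates or oxygen use that the form does not collect.
- The ethics committee abstract says hospital records will be used to fill the data sheet, so imaging dates and oxygen use might be recovered there. They might, for some patients. But no section schedules a repeat image, so criterion 3 would rest on whatever imaging was done in routine care.
- The planning rates of 0.70 and 0.90 are for cure, which is not stated to be this five-part endpoint. This stands, and the comparison with 0.90 is conditional on it.

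A reader might also infer more than the documents support:

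- *Mild patients cannot meet criterion 4 either.* They can. It also covers complications, which may arise from COVID-19. Its weakness is the lack of a dated entry.
- *If criterion 3 is waived, mild patients have durations near zero.* This does not follow. Criterion 1 needs three days of normal temperature and criterion 2 still applies. The time origin is also not fixed: the form holds dates of symptom onset, positivity and admission.
- *Around half the cohort has clear lungs.* The documents give no such share. In a hospital cohort it could be low, and at f = 0.10 the power loss is small.

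**Conclusion.** The point holds. On the natural reading that all five criteria are required, eligible patients with normal baseline imaging can never reach the primary event. Criterion 3 cannot be dated from the Case Record Form for any patient, and criteria 4 and 5 are not fully recorded. This is a fault in a rule the protocol states and in the form meant to supply it, so it should be corrected in both.

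Its size depends on f, which is unknown. Improvement is capped at 1 − f, the planned 0.90 in non-A is unreachable above f = 0.10 if cure means this endpoint, and absolute rates and durations are distorted for any f above zero. Equal f leaves the relative risk at 0.778 and costs power, from 99.6% to 87.0% at f = 0.20 and 59.6% at f = 0.40.

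It is tempting to conclude that the blood-group comparison must be biased. That goes too far: the relative risk is biased only if imaging status differs between A and non-A, which the documents do not show.

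**What to change.** In the protocol:

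- State that all retained criteria must be met together, and from which date time is counted.
- Base the primary endpoint on the protocol's own criteria 1, 2 and 5, derived from the daily temperature, symptom and saturation entries. Say which yes/no symptom entries decide criterion 2, and which of the three normal-temperature days dates the event.
- Remove criterion 3 from the primary endpoint, or keep it only as a secondary descriptor in patients with baseline lesions and a dated repeat image.
- Remove criterion 4 from the primary endpoint, or record it with a date.
- Keep all enrolled patients in the primary analysis. Report by blood group how many already meet the definition at entry, and exclude them only in a sensitivity analysis. Their number is unknown, and dropping them from the main analysis could remove much of the cohort.

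In the Case Record Form, add a daily yes/no box for being on oxygen.

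The cost is protocol and form wording plus one tick-box, with no new procedure. The downside is small: the primary endpoint no longer includes radiological improvement.

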**5. UTILIZATION OF RESULTS:**

This study will observe the benefit of combined Doxycycline and Ivermectin on confirmed covid 19 patient. The study result will be compared with other trials in home and abroad.

**8. FLOW CHART of Study workup:**

| Sl No | **Activities** |  |  |  |  |  |  |
| --- | --- | --- | --- | --- | --- | --- | --- |
|  |  | **1^st^** | **2^nd^** | **3^rd^** | **4^th^** | **5^th^, to 15^th^** | **16^th^** |
| 1 | **Recruitment and training of the field staff** |  |  |  |  |  |  |
| 2 | **Pretesting and finalization of the questionnaire** |  |  |  |  |  |  |
| 3 | **Consultative meeting** |  |  |  |  |  |  |
| 4 | **Data collection** |  |  |  |  |  |  |
| 5 | **Data entry and editing** |  |  |  |  |  |  |
| 6 | **Data analysis and draft report writing** |  |  |  |  |  |  |
| 7 | **Dissemination of Results** |  |  |  |  |  |  |

1. **ETHICAL IMPLICATIONS**

The following points will be considered during the study:

1. Patients (subjects) and key relatives were clearly informed about the scope and limitation of the study.

2. Written consent will be obtained from the patients (subjects) or from parents if patient (subject) is unable to give reliable information.

3. Confidentiality of the patients (subjects) about personal information was strictly maintained.

4. The study will not be causing any environmental hazard.

**Abstract summary for Ethical Committee**

This hospital based Experimental study will be carried out in COVID-19 Unit, Dhaka Medical College Hospital for the duration of 4 months. Consecutive confirmed COVID-19 patients with mild to moderate severity whom will be enrolled from June, 2000 to august, 2000. Total 400 cases will be enrolled for the research. They will be followed up for at least 30 days or hospital discharge which one is longer.

1. By the following under mentioned steps confidentially will be maintained:

- Research data will be coded
- Data will be stored in a locked cabinets
- Only research personnel will be allowed to access data
- There is no physical, psychological, social and legal risk during physical examination. Proper consent will be taken.
- For safeguarding confidentially and protecting anonymity each of the patient will be given and ID no.
- A signed informed consent will be taken from the patient/patients guardians convincing that privacy of the patient will be maintained and he/she will not be compensated for loss of work time if they want.
- A data should (enclosed) be prepared for which a short interview of 15-30 minutes will be required
- Use of hospital records (indoor) will be needed to fill up the patients’ data sheet.

2. Consent form will be a written statement

1. A brief interview regarding study variables will be collected from the participants.

**Circle the appropriate answer to each of the following**

**(If not Applicable write NA).**

| **1. Source of population:** |  |  | **4. Are subjects clearly informed about** |  |  |
| --- | --- | --- | --- | --- | --- |
| a) Patients | Yes | No | a) Nature and purposes of study | Yes | No |
| b) Healthy subjects | Yes | No | b) Procedures to be followed including alternatives used | Yes | No |
| c) Minors or persons under guardianship | Yes | No | c) Physical risks | Yes | No |
| **2. Does the study involve:** |  |  | d) Private questions | Yes | No |
|  |  |  | e) Invasion of the body | NA | |
| a) Physical risks to the subject | Yes | No | f) Benefits to be derived | Yes | No |
| b) Social Risks | Yes | No | g) Right to refuse, to participate or to withdraw from study | Yes | No |
| c) Psychological risks to subjects | Yes | No | h) Confidential handing of data | Yes | No |
| d) Discomfort to subjects | Yes | No | i) Compensation where there are risks or loss of working time or privacy is involved in any particular procedure | NA | |
| e) Invasion of the Body | Yes | No |  |  |  |
| f) Invasion of privacy | Yes | No |  |  |  |
| g) Disclosure of information damaging to subjects or others | Yes | No |  |  |  |
| **3. Does the study involve:** |  |  | **5. Will signed consent form/verbal Consent be required:** |  |  |
| a) Use of records, (hospital, medical, death, birth or other). | Yes | No | a) From Subject | Yes | No |
| b) Use of fetal tissue or aborts | Yes | No | b) From parent or guardian (if Subjects are minors) | NA | |
| c) Use of organs or body fluids | Yes | No | **6. Will precautions be taken to protect anonymity of subjects.** | Yes | No |

**Part-G**

**Abstract For National Research Ethics Committee (NREC)**

**Project Title:**

Project Title: **Association of ABO blood groups with presentation and outcomes of confirmed SARS CoV-2 infection: A prospective study in the largest COVID-19 dedicated hospital in Bangladesh**

# Purpose of the study:

To observe the susceptibility of COVID-19 infection in association with ABO blood groups..

**Methodology**:

1. **METHODOLOGY:**

Study type: Prospective cohort

Sample size:

Proportions to cure from COVID-19 by day-12 in group-1(blood group A) and group-2 (blood group Assuming expected B, O, AB) are 0.70 and 0.90 respectively. Thus we need a total of 378 samples at 1:2 ratio, and, that would provide a power of at least 90% at two tailed test where p value less than 0.05 to detect significant difference between the groups. Considering 10% dropout, we need 416 samples in total.

$$n=\frac{r+1}{r}\frac{p^{*}\left( 1-p^{*} \right){(Z_{\beta}+Z_{\frac{\alpha}{2}})}^{2}}{{{(p}_{1}- p_{2})}^{2}}$$

r = ratio of group-1 and group - 2

p*= Average of proportion

Z_α/2_ = Level of significance

Z_β_ = Power of the test

p_1_ - p_2_= Effect size

p_1_ = Proportion in group - 1

p_2_ = Proportion in group - 2

**Sampling: Consecutive sampling.**

Estimated study date: June, 2020

Estimated primary completion date, August 2020

Estimated study completion date: September, 2020

**Inclusion Criteria:**

- At least 18 years of age
- COVID-19 infection, confirmed by polymerase chain reaction (PCR) test
- Mild to moderate COVID-19 infection
- Able to provide informed consent

**Exclusion Criteria:**

- Not willing to participate.
- Discontinue duties for any reason during the specified period
- Presence of haemoglobinopathies or other blood disorders.

**Research instruments:**

1. Informed consent form.

2. Case record form

**Primary Outcome Measure:**

- 1. Duration required to have clinical improvement

[Time Frame: 1 months]

**Secondary Outcome Measure:**

1. Conversion to the next level of severity

Time Frame: 1 month]

1. Persistent positivity 14 days after initial positivity

[Time Frame: 14 days]

1. Severity of the disease

[Time Frame: 1 month]

1. Development of post COVID syndrome

[Time Frame: 1 month]

**Data collection technique:**

Data will be collected by assigned trained data collectors (Physician).

Patient will be enrolled according to defined inclusion and exclusion criteria in the current research. Informed written consent will be obtained from the participants. Each participants participating in the trial will be uniquely identified, and information such as his name, address is recorded in the trial 'subject number list'.

**Data analysis**:

To compare the groups one way ANOVA was done for continuous variable, Chi square for categorical variables. For outcome assessment relative risk (RR) with 95% CI was measured for qualitative variable categorizing blood group-A and non-A (Group-B, AB, O). Survival analysis by Kaplan-Meier curve was done for the duration of recovery.

**Observation and Results:**

Result of the study and statistical analysis will be presented by tables, figures, graphs, diagrams, charts and photographs. All these would have own legends (i.e. title) and will be serially numbered.

**Discussion:**

Discussion will be done on the basis of result obtained from the study and comparing with similar studies done at home and abroad.

**Summary:**

Summarization will be drawn after discussion.

**Conclusion:**

Conclusion would be drawn depending upon the results and discussion

**Conflict of interest:** None

**Conflict of interest:** None

Project Title: **Association of ABO blood groups with presentation and outcomes of confirmed SARS CoV-2 infection: A prospective study in the largest COVID-19 dedicated hospital in Bangladesh**

**Case Record Form**

**Patient ID**: ……………

**Demography**

1. Name: 2. Age: 3. Sex: M / F

4. Address:

5. **Epidemiological link**: Y / N

5. Mobile No:

6. Residency: Urban / Rural

7. Smoker: Y / N

8. Marital Status: Married / Single

9. Education: Literate / Illiterate

Date of starting symptoms

Date of becoming Covid positive

Hospital Admission Date

**Clinical Feature**

| Trait |  | Follow-up  Yes-1, No-2 | | | | | | | | | | | | |
| --- | --- | --- | --- | --- | --- | --- | --- | --- | --- | --- | --- | --- | --- | --- |
|  | On Admission | D2 | D3 | D4 | D-5 | D-6 | D-7 | D-8 | D-9 | D-10 | D-11 | D-12 | D-13 | D-14 |
| Fever | Yes No |  |  |  |  |  |  |  |  |  |  |  |  |  |
| Cough | Yes No |  |  |  |  |  |  |  |  |  |  |  |  |  |
| Running nose | Yes No |  |  |  |  |  |  |  |  |  |  |  |  |  |
| Sputum | Yes No |  |  |  |  |  |  |  |  |  |  |  |  |  |
| Respiratory distress | Yes No |  |  |  |  |  |  |  |  |  |  |  |  |  |
| Sore throat | Yes No |  |  |  |  |  |  |  |  |  |  |  |  |  |
| Hoarseness of voice | Yes No |  |  |  |  |  |  |  |  |  |  |  |  |  |
| Chest pain | Yes No |  |  |  |  |  |  |  |  |  |  |  |  |  |
| Diarrhoea | Yes No |  |  |  |  |  |  |  |  |  |  |  |  |  |
| Vomiting | Yes No |  |  |  |  |  |  |  |  |  |  |  |  |  |
| Anosmia | Yes No |  |  |  |  |  |  |  |  |  |  |  |  |  |
| Anorexia | Yes No |  |  |  |  |  |  |  |  |  |  |  |  |  |
| Headache | Yes No |  |  |  |  |  |  |  |  |  |  |  |  |  |
| Confusion | Yes No |  |  |  |  |  |  |  |  |  |  |  |  |  |

**Subsequent follow up**

| Trait | Follow-up  Yes-1, No-2 | | | | | | | | | | | | | | | |
| --- | --- | --- | --- | --- | --- | --- | --- | --- | --- | --- | --- | --- | --- | --- | --- | --- |
|  | Day-15 | D16 | D17 | D18 | D-19 | D-20 | D-21 | D-21 | D-23 | D-24 | D-25 | D-26 | D-27 | D-28 | D-29 | D-30 |
| Fever |  |  |  |  |  |  |  |  |  |  |  |  |  |  |  |  |
| Cough |  |  |  |  |  |  |  |  |  |  |  |  |  |  |  |  |
| Running nose |  |  |  |  |  |  |  |  |  |  |  |  |  |  |  |  |
| Sputum |  |  |  |  |  |  |  |  |  |  |  |  |  |  |  |  |
| Respiratory distress |  |  |  |  |  |  |  |  |  |  |  |  |  |  |  |  |
| Sore throat |  |  |  |  |  |  |  |  |  |  |  |  |  |  |  |  |
| Hoarseness of voice |  |  |  |  |  |  |  |  |  |  |  |  |  |  |  |  |
| Chest pain |  |  |  |  |  |  |  |  |  |  |  |  |  |  |  |  |
| Diarrhoea |  |  |  |  |  |  |  |  |  |  |  |  |  |  |  |  |
| Vomiting |  |  |  |  |  |  |  |  |  |  |  |  |  |  |  |  |
| Anosmia |  |  |  |  |  |  |  |  |  |  |  |  |  |  |  |  |
| Anorexia |  |  |  |  |  |  |  |  |  |  |  |  |  |  |  |  |
| Headache |  |  |  |  |  |  |  |  |  |  |  |  |  |  |  |  |
| Confusion |  |  |  |  |  |  |  |  |  |  |  |  |  |  |  |  |

**Obsrvation**

| Trait |  | Follow-up  Yes-1, No-2 | | | | | | | | | | | | |
| --- | --- | --- | --- | --- | --- | --- | --- | --- | --- | --- | --- | --- | --- | --- |
|  | On Admission | D2 | D3 | D4 | D-5 | D-6 | D-7 | D-8 | D-9 | D-10 | D-11 | D-12 | D-13 | D-14 |
| Temperature |  |  |  |  |  |  |  |  |  |  |  |  |  |  |
| Pulse rate |  |  |  |  |  |  |  |  |  |  |  |  |  |  |
| BP |  |  |  |  |  |  |  |  |  |  |  |  |  |  |
| Respiratory Rate |  |  |  |  |  |  |  |  |  |  |  |  |  |  |
| Oxygen saturation |  |  |  |  |  |  |  |  |  |  |  |  |  |  |
| Co- Morbidity | DM/HTN/ IHD/ HF/ CKD/CLD/Asthma/COPD/Malignancy/ CTD | | | | | | | | | | | | | |

**Subsequent observation:**

| Trait | Follow-up  Yes-1, No-2 | | | | | | | | | | | | | | | |
| --- | --- | --- | --- | --- | --- | --- | --- | --- | --- | --- | --- | --- | --- | --- | --- | --- |
|  | Day 15 | D16 | D17 | D18 | D-19 | D-20 | D-21 | D-22 | D-23 | D-24 | D-25 | D-26 | D-27 | D-28 | D-29 | D-30 |
| Temperature |  |  |  |  |  |  |  |  |  |  |  |  |  |  |  |  |
| Pulse rate |  |  |  |  |  |  |  |  |  |  |  |  |  |  |  |  |
| BP |  |  |  |  |  |  |  |  |  |  |  |  |  |  |  |  |
| Respiratory Rate |  |  |  |  |  |  |  |  |  |  |  |  |  |  |  |  |
| Oxygen saturation |  |  |  |  |  |  |  |  |  |  |  |  |  |  |  |  |

**Investigations Profile**

| **Trait** | **Value** |  |  |  |  |  |
| --- | --- | --- | --- | --- | --- | --- |
|  | **Admission** | **D-3** | **D-5** | **D-7** | **D-10** | **D-14** |
| **Hb** |  |  |  |  |  |  |
| **WBC** |  |  |  |  |  |  |
| **Neutrophil** |  |  |  |  |  |  |
| **Lymphocyte** |  |  |  |  |  |  |
| **Platelet** |  |  |  |  |  |  |
| **ESR** |  |  |  |  |  |  |
| **CRP** |  |  |  |  |  |  |
| **RBS** |  |  |  |  |  |  |
| **Creatinine** |  |  |  |  |  |  |
| **SGPT** |  |  |  |  |  |  |
| **D-Dimer** |  |  |  |  |  |  |
| **Na** |  |  |  |  |  |  |
| **K** |  |  |  |  |  |  |
| **ECG** |  |  |  |  |  |  |
| **Covid-19**  **RT-PCR** |  |  |  |  |  |  |

